## Abstract

**Background:**

Midlife and older women who experience intimate partner violence (IPV) often have less access to supports and services than younger women. There is far less focus on research and supports for midlife and older women compared to younger women experiencing IPV, and often, neither elder abuse nor IPV services meet their needs. Few interventions are available to meet the needs of midlife and older women.

**Objective:**

The goal of this randomized controlled trial is to test the effectiveness of an advocacy intervention for midlife and older women who experience IPV and to learn from the experiences of those who implement and participate in the program.

**Methods:**

This trial is a 2-arm, unblinded, parallel, pragmatic randomized controlled trial with a qualitative component. Eligible participants will be women who live in the Maritime provinces of Canada (New Brunswick, Nova Scotia, and Prince Edward Island), who are in midlife and older (aged approximately ≥50 years), and who are currently in a relationship with an abusive partner or have recently left an abusive partner. Facilitators will be trained to deliver the intervention. The intervention will be entirely virtual and will consist of 2 components: (1) an empowerment component, which will involve sharing resources and information with the women; and (2) a social support component, which will include providing support and encouragement to women for 12 weeks. Quantitative effectiveness data will be collected from all trial participants at baseline, 3 months after the intervention, and 9 months after the intervention about the incidence and severity of IPV, physical and mental health, and safety behaviors and strategies. Qualitative interviews will be conducted with the facilitators and intervention group participants. Control group participants will receive a static, nontailored version of the advocacy intervention for midlife and older women (AIM) intervention materials after baseline data collection.

**Results:**

A total of 12 facilitators have been trained to deliver the AIM intervention to trial participants. Participant recruitment and data collection will be completed in January 2025. Data analysis will continue throughout the data collection period, and the results will be disseminated by December 2025.

**Conclusions:**

This research will result in the adaptation and testing of a program to support and empower midlife and older women in the Maritime provinces of Canada who experience IPV.

**Trial Registration:**

International Standard Randomized Controlled Trial Registry ISRCTN30646991; https://doi.org/10.1186/ISRCTN30646991

**International Registered Report Identifier (IRRID):**

DERR1-10.2196/57886

## Introduction

### Background and Rationale

Intimate partner violence (IPV) is widely recognized as a major public health concern globally [1] and in Canada, with 1 in every 10 adults aged ≥65 years experiencing some form of abuse each year [2]. We use the term IPV to refer to any type of abusive behavior (eg, emotional, verbal, physical, sexual, or financial) that occurs between intimate partners, such as spouses, those living in a common-law relationship, or in a dating relationship. While our knowledge is far less complete on IPV among older versus younger women, a mistaken assumption is that IPV ceases with age [3]. Prevalence studies have shown that between 15% and 30% of older women report IPV at some point in their lives [4-7]. Incidence studies have shown that 8.6% of women currently in partnerships experienced IPV since reaching the age of 55 years [8]; 3.5% of women aged ≥65 years experienced IPV in the past 5 years, with 2.2% in the past year [4]; and 5.5% of women aged between 50 and 64 years experienced IPV in the past 2 years [9]. In a study of coroners’ files of homicide by individuals aged ≥65 years, 89% of homicide survivors were female, and of these, 93% were current or former spouses of male perpetrators [10]. It is generally recognized that IPV among older women is underestimated.

There is far less focus on research and supports for midlife and older women compared to younger women experiencing IPV, and often, neither elder abuse nor IPV services address their unique needs. Researchers define midlife as a pivotal time in the life span, representing the transition from earlier to later periods of life during which individuals are balancing multiple roles, life transitions, and opportunities and challenges [11]. Midlife is generally viewed as spanning from the ages of 40 to 60 years [11]. Midlife is viewed as a bridge between generations and can involve multiple caregiving responsibilities (eg, grandchildren, adult children, and aging parents), career development and retirement planning, changes in family leadership, and changes in health status (eg, developing chronic illnesses) [11]. During midlife, women often juggle multiple demands. People providing elder abuse services often are not equipped to support women from a gendered and relational lens [12], and those providing family violence services often focus on meeting the needs of girls, young women, and women with dependent children [13]. Thus, the needs of midlife and older women who experience IPV may not be met by the assistance of those working in elder abuse or IPV services. In addition, initiatives that offer IPV support and services to older women in Canada do not necessarily implement formal program evaluations, and therefore, information about the effectiveness of these initiatives is lacking [14].

Women have unique needs and experiences and require individualized help to receive the support they need. In a recent research study conducted by our team, we interviewed midlife and older women and found many groups of women, including francophone women, new immigrants (eg, from Arabic-speaking countries), Black women, and people living in rural places with limited access to services, have unique needs [15]. Research suggests that other populations considered vulnerable in Canada are also at increased risk of experiencing IPV, such as Indigenous women, gender and sexual minority groups, and people living with disabilities [16]. Women considered vulnerable and women with multiple vulnerable identities are at an increased risk of experiencing IPV due to them being exposed to multiple forms of systemic oppression (eg, racism, agism, and ableism), making it difficult to break the cycle of violence [17].

Given that many existing services are not appropriate to meet the unique needs of older women, there is an emergent emphasis on supports that do address the unique preferences and situations, or “victim-centered supports” [18,19]. There are few published studies about initiatives focused specifically on IPV and older women [14]. While a feminist lens is often used in research and with practitioners working with abused women and girls, gender-based analysis is often neglected by scholars and practitioners working with or for abused midlife and older women. In this research, we will use an intersectional approach to consider how various social factors (eg, age, gender, language, race, ethnicity, culture, and geographic region) intersect to impact women’s risk of IPV exposure and their experiences of violence, their ability to seek help and access services, as well as their overall health and quality of life [20].

### Objectives

The goal of this randomized controlled trial (RCT) with a qualitative component is to test the effectiveness of the 2 components of an advocacy intervention for midlife and older women (AIM) that has been adapted to support midlife and older women who have experienced IPV and to learn from the experiences of those who will implement and participate in the program. This research will support the adaptation, scale-up, and spread of the program to support and empower women in Canada in midlife and older who experience IPV to improve their health and quality of life.

## Methods

### Trial Design

This trial is a 2-arm, unblinded, parallel, pragmatic RCT [21] registered in the International Standard Randomized Controlled Trial Registry (ISRCTN30646991). This protocol is reported according to the SPIRIT (Standard Protocol Items: Recommendations for Interventional Trials) guidelines [22]. The intervention has been modeled using the Template for Intervention Description and Replication checklist [23], and the results will be reported according to the CONSORT (Consolidated Standards of Reporting Trials) statement for RCTs [24]. Figure 1 displays the CONSORT flow diagram for this RCT.

**Figure 1 figure1:**
[figure not shown]
CONSORT (Consolidated Standards of Reporting Trials) flow diagram.

### Study Setting

Participants will be recruited from the 3 Maritime provinces of Canada (New Brunswick, Nova Scotia, and Prince Edward Island). As the program will be delivered virtually, we are not restricted to a certain number of sites. Our rationale for including the Maritime provinces for this study is that the members of our research team are located within the Maritime provinces, and we have extensive professional and personal networks that will help to support the success of the research. The Maritime provinces are among the Canadian provinces with the highest proportion of adults aged ≥65 years [25]. In addition, New Brunswick is the only Canadian province that is officially bilingual and represents a unique opportunity to include both anglophone and francophone participants from the same geographic region [26].

### Eligibility Criteria

The following inclusion criteria will be used to determine if women are eligible to be enrolled in the trial. The potential participants are those who self-identify as a woman; are in midlife and older (aged approximately ≥50 years); are currently living in the Maritime provinces; can participate in an interview in either English or French; and are currently in a relationship with an abusive partner or have recently left an abusive partner within the last year, including a same-sex partner.

In a recent systematic review [27], our team used the theoretical concepts of reclaiming self-theory and the four levels of prevention [28-31] to classify IPV interventions into the categories of (1) preventing IPV, (2) identifying and documenting IPV, (3) supporting women while living with or leaving an abusive partner, and (4) supporting women after leaving an abusive partner. The intervention used in this trial will target women in category 3 as it is designed to empower women to make decisions and take action related to the abuse they are experiencing or have recently experienced.

The dynamics of abusive relationships are such that leaving an abusive partner is often a process that involves leaving and returning multiple times [32]. During this process, the woman may reach out to available services, such as outreach services, or live in a transition house or other form of safe housing. Thus, the participants may have already contacted IPV services and may be using various forms of services or initiatives during the course of this study. Given that our research team will not be interfering with the supports and services that the participants are already using during their participation in the study, this study aligns with the tenets of a pragmatic trial [33]. Our team has had success recruiting older women experiencing IPV who had already accessed services, but we have had challenges recruiting older women in the region who have never contacted an organization for support [14]. The intervention is designed to provide information about other resources and supports available to women and to encourage women to use these services; therefore, it is not a concern that the women access and use other supports during our study.

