### Random Assignment of Interventions

REDCap (Research Electronic Data Capture; Vanderbilt University) software will be used to store and manage the data collected from participants. REDCap is a web-based software application that securely stores research data [42]. The random allocation sequence was generated using REDCap [42]. The research coordinator developed an allocation table that included each option for random assignment that was stratified by the province of residence. This involved creating an Excel (Microsoft Corp) table with each intervention option (ie, intervention and control) in one column and province of residence (ie, New Brunswick, Nova Scotia, and Prince Edward Island) in another column. We wanted to ensure that an equal number of participants were randomized to the intervention and control group within each province in a balanced manner. Therefore, there were 6 study options uploaded to the software. Once the allocation table was uploaded to REDCap, it was locked and could not be modified.

REDCap will be used to randomize the participants. After a participant has completed the baseline surveys, the researcher will press the “randomize” button to determine the participant’s group allocation. While assignment to the groups is random, once assigned, participants are not blinded to their group. The researcher will inform each participant of the group they are allocated to at the end of the baseline interview. The research staff (research coordinator and research assistant) will be responsible for screening, consenting, enrolling, and using Recap’s randomization module to allocate participants to their study group.

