### Outcomes Measured

Research staff will collect quantitative effectiveness data from participants by telephone or video call at 3 time points: baseline, 3 months, and 9 months. Research staff will schedule a meeting by telephone or Zoom (Zoom Video Communications) to collect the survey responses from participants verbally. Table 1 details the survey information to be collected directly from participants.

**Table 1 table1:** Quantitative measures.

Quantitative measure collected	Time point for data collection			Explanation
	Baseline	3 months	9 months	
Screening questions	✓			Age, province of residence, and description of the stage of their relationship with their abusive partner
Demographic information	✓			Education, marital status, and diversity characteristics (eg, immigrant status, francophone status, ethnic status, and rural status)
WEB^a^	✓	✓	✓	To measure women’s experiences of feeling fearful and controlled by their abusive partner [43]
DCS^b^	✓	✓	✓	To measure the conflict (ie, difficulty) that women endure in making decisions about leaving their abusive relationship [44]
IPV^c^ strategies index	✓	✓	✓	To measure the different types of IPV strategies that women are using to keep themselves safe in their abusive relationship [45]
SF-12v2^d^	✓	✓	✓	To measure quality of life [46]
CES-D^e^	✓	✓	✓	To measure depressive symptoms [47]
ISEL^f^	✓	✓	✓	To measure perceived social support [48]

^a^WEB: Women’s Experiences of Battery Scale.

^b^DCS: Decisional Conflict Scale.

^c^IPV: intimate partner violence.

^d^SF-12v2: Short Form Health Survey.

^e^CES-D: The Center for Epidemiologic Studies Depression Scale.

^f^ISEL: The Interpersonal Support Evaluation List.

Primary outcomes include (1) physical and mental health, (2) knowledge about IPV, and (3) safety strategies. Physical and mental health will be assessed using the following scales: Short Form Health Survey [46], Centre for Epidemiologic Studies Depression Scale [47], and Interpersonal Support Evaluation List [48]. Knowledge about IPV and safety strategies will be measured using the following scales: the Women’s Experiences of Battery Scale [43], Decisional Conflict Scale [44], and Intimate Partner Violence Strategies Index [45].

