#### Confidentiality and Anonymity

All study data will be kept confidential, and the participants’ identity (eg, names and identifying information) will not be made known in any reports of the results. A participant ID number will be used for any quotes in reporting qualitative results. Qualitative interviews will be recorded on the research coordinator’s secure laptop. The transcription function in Microsoft Word will be used to create a draft transcript that will then be edited by the research team members. Once a transcript is checked and edited by a research team member, the interview transcripts and the quantitative data will be shared among the team members using OneDrive, a secure, password-protected file-sharing system hosted by Dalhousie University. No hard copies of any study documents that could identify a participant will be retained.

The digital recordings will be kept only until the transcript is prepared, and then, the recording will be destroyed. Qualitative data, numerical key codes, and contact information of the participants will be retained by the co–principal investigators on a password-protected computer and on the OneDrive systems at Dalhousie University and the University of New Brunswick. These data will be destroyed 5 years after the publication of study results. Each participant will be given the option of allowing the co-principal investigators to retain the deidentified quantitative data indefinitely to be used in potential future research studies or for teaching purposes (eg, in a course with content on family violence). Providing this consent is not required for inclusion in the study.

This study focuses on midlife and older women who are currently experiencing IPV and are either living with an abusive partner or are in the process of leaving an abusive partner. There are different laws regarding the duty to report elder abuse in different provinces where we will be collecting data, and we will follow the procedure in each province. However, the issues about when to report typically are focused on the situations in which people do not have the physical or mental capacity to protect themselves or make their own decisions. If in the process of conducting data collection, the abuse of a child or an adult in need of protection is disclosed, the facilitator will contact the appropriate child protection or adult protection services in the location where the data are being collected.

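### The enrolled population is described inconsistently across sections, and relationship stage, recorded at screening and plausibly prognostic, is not used in the stated analysis

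*Protocol article*

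**What the plan says.** **Who may enter.** Under Eligibility Criteria, women qualify if they "are currently in a relationship with an abusive partner or have recently left an abusive partner within the last year". The Abstract agrees in including women who have recently left.

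**Whom the intervention is for.** The same section classifies interventions for IPV into four categories. The last two are "supporting women while living with or leaving an abusive partner, and (4) supporting women after leaving an abusive partner". It then states: "The intervention used in this trial will target women in category 3 as it is designed to empower women to make decisions". That sentence goes on to say that women are also empowered to "take action related to the abuse they are experiencing or have recently experienced". The following paragraph describes leaving as a process that may be repeated.

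**How the population is described elsewhere.** Confidentiality and Anonymity says the study concerns women with current IPV who "are either living with an abusive partner or are in the process of leaving an abusive partner".

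**What is done with stage.** Table 1 (Outcomes Measured) lists, among the baseline screening questions, a "description of the stage of their relationship with their abusive partner". The allocation table is one "that was stratified by the province of residence" (Random Assignment of Interventions). Statistical Analysis names chi-square or Fisher exact tests for categorical data and repeated measures analysis of variance for continuous variables, comparing the two groups at 3 and 9 months. It mentions neither stage nor province.

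**The concern.** A woman who left ten or eleven months ago and is no longer being abused meets the eligibility criterion. She does not fit the description in Confidentiality and Anonymity. Whether she counts as category 3 or category 4 cannot be settled from the text, because no boundary between the two is given. A reader of the results would not know which population the pooled estimate describes.

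Stage also bears on the outcomes. Table 1 describes the Decisional Conflict Scale (DCS) as capturing how hard it is to decide about leaving, and the IPV strategies index as capturing what a woman does to stay safe within the relationship. Both measure primary outcomes. For a woman who has already left, a low strategies score may reflect less need rather than less benefit, and decisional conflict about leaving may have a different meaning. Stage is therefore a plausible predictor of these scores and of their change. Leaving it out of the between-arm comparison gives up some precision and makes the pooled means harder to read.

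**Working it through.** **1. The texts side by side.**

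| Place | Current relationship | In the process of leaving | Left within the last year |
|---|---|---|---|
| Abstract, Methods | yes | not named separately | yes (recently left; no time limit given) |
| Eligibility Criteria, inclusion | yes | not named separately | yes |
| Eligibility Criteria, target category | yes | yes | partly: recent abuse is covered, but after leaving is a separate category with no boundary given |
| Confidentiality and Anonymity | yes (living with the partner) | yes | not named; current IPV is stated |

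The last row does not match the first two. The third row leaves the boundary open.

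**2. The plan's own sample size.** Sample Size gives 30 per arm, 15% attrition, and 70 recruited (35 per arm). Check: 60 / 0.85 = 70.6 in total, or 30 / 0.85 = 35.3 per arm; and 70 × 0.85 = 59.5. The stated 70 reproduces to within rounding. I use 35 and 30 per arm below.

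**3. Chance imbalance in stage.** The article gives no share of women who have already left, so p = 0.2, 0.3 and 0.5 are assumptions. With independent binomial counts X1 and X2 in arms of size n, I sum the joint probabilities over all pairs with |X1 − X2| ≥ 0.20n, that is, 7 women when n = 35 and 6 women when n = 30.

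| Assumed share already left | n = 35 per arm | n = 30 per arm |
|---|---|---|
| 0.2 | 0.051 | 0.075 |
| 0.3 | 0.089 | 0.120 |
| 0.5 | 0.120 | 0.155 |

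**4. What such an imbalance would do.** Suppose the outcome, or its change, differs by D = 0.5 to 0.8 SD between stages (assumed; the article gives no figure). A 20-point imbalance moves the arm difference by 0.20 × D, which is 0.10 to 0.16 SD. The standard error of the arm difference is √(2/35) = 0.24 SD, or √(2/30) = 0.26 SD. The shift is therefore below one standard error.

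**5. What adjustment would gain.** A binary covariate with share p and effect D explains R² = p(1 − p)D² of the variance, and the standard error is multiplied by √(1 − R²).

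| p | D = 0.5: R², SE reduction | D = 0.8: R², SE reduction |
|---|---|---|
| 0.2 | 0.040, 2.0% | 0.102, 5.3% |
| 0.3 | 0.053, 2.7% | 0.134, 7.0% |
| 0.5 | 0.063, 3.2% | 0.160, 8.3% |

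For scale, take 30 per arm and a true difference of 0.5 SD (assumed; two-sided 5% test, normal approximation). Power is 0.49 unadjusted. With p = 0.5 it is 0.52 when adjusted for D = 0.5 and 0.56 when adjusted for D = 0.8.

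**The case against.** The case against has real force, and most of it stands.

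- **Target category.** A reader might infer that women who left up to a year ago fall outside the category the intervention targets. The text does not support that. The target sentence expressly reaches recently experienced abuse, leaving is called a repeated process, and no time boundary separates categories 3 and 4. The one-year limit can be read as the authors' meaning of recent.
- **Two populations.** A reader might also infer that the framework says these women need different interventions. It classifies interventions from a review and says no such thing. Components of AIM describes individually tailored support that includes processing past abuse and help with legal proceedings, which suits women who have left.
- **Stratification.** Using province alone is a legitimate choice with 70 women; adding binary stage would double three strata to six. Chance imbalance between randomised groups is not bias, and an unadjusted test's standard error already allows for it.
- **Silence on covariates.** A condensed article may leave covariates to an analysis plan that is not shown. Failure to name stage is therefore not an error in itself.
- **The confidentiality sentence.** It introduces the duty to report abuse and is not an eligibility rule. Enrolment does not depend on it.

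What this does not answer is that the article gives two descriptions of its population that do not agree and leaves the category boundary open. Nor does it remove the benefit of using a variable that is already collected and tied by the article's own wording to two primary-outcome scales.

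**Conclusion.** The point holds as one of consistency and modest efficiency. Eligibility Criteria and Confidentiality and Anonymity need to be reconciled, with the line between leaving and after leaving made explicit, so that the conclusions match the women enrolled. Using stage in the comparison of continuous outcomes is worthwhile and nearly free. The likely gain is a standard error about 2% to 8% smaller, with protection against a stage imbalance of 20 points or more that has probability 0.05 to 0.16.

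These figures rest on an assumed 20% to 50% of women having left and an assumed stage effect of 0.5 to 0.8 SD; neither is in the article. A smaller effect, or one already captured by the baseline score, would mean a smaller gain. The documents do not support reading this as a correction of bias or of a faulty stratification. The remark that imbalance is not bias concerns the groups as randomised; the attendance rule for including intervention-arm data is a separate matter.

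**What to change.** 1. Keep the inclusion window and the locked allocation table.
2. Reconcile Eligibility Criteria with Confidentiality and Anonymity so that both describe the population actually enrolled, and state how women who left within the last year relate to categories 3 and 4.
3. Code the screening answer as a binary baseline variable: with the partner or in the process of leaving, versus left within the last year. Fix the coding rule before any comparison by arm.
4. Include this variable and province, the stratification factor, as covariates in the between-arm comparisons of continuous outcomes. If baseline is one of the repeated measures, let stage and province interact with time; otherwise they do not adjust the difference in change.
5. Show each arm's results by stage descriptively, in particular for the DCS and the IPV strategies index, without subgroup tests.
6. Word the conclusions to the enrolled population.

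**Cost:** some rewording, no new data, and a few degrees of freedom (one for stage and two for the three provinces at each time point, out of about 60 women). The stage subgroups will be too small for anything beyond description.
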